#### Interim analyses {21b}

Interim analyses are not planned.

#### Methods for additional analyses (e.g., subgroup analyses) {20b}

Further group analyses will be stratified by frequency of AP ≤ 2/week and severity of CAD (> 1 vessel affected). As dyspnea is a common symptom of CAD which is not used as a criterion for the classification of typical angina pectoris [2], we will also analyze the pre-specified subgroup of people presenting with dominant dyspnea as an equivalent of AP.

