**Design and methods:**

The PLA-pCi-EBO-pilot-trial is a prospective, multi-center, randomized, controlled investigator-initiated pilot trial to study the effect of visual demonstration of successful PCI on quality of life (QoL) and angina pectoris (AP) in patients with symptomatic stable CAD/CCS. All patients with stable CAD/CCS and successful PCI will be screened. One hundred forty four patients with a frequency of AP ≥ 2/week will be randomized 1:1 stratified for AP frequency > 1/day. The control group will receive the common written procedural report on the procedure. Patients in the intervention group will additionally be given a printout picture of their coronary angiogram both before and after PCI. Primary endpoints are change in the Seattle Angina Questionnaire (SAQ)-derived QoL score 1 and 6 months after PCI. Secondary endpoints are changes in other SAQ-derived scores and dyspnea (NYHA score) 1 and 6 months after PCI.

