#### Sample size {14}

The study is designed and powered as a pilot trial to allow for precise parameter estimation for a subsequent confirmatory study. There is sparse comparable data to calculate effect size estimations for the kind of intervention employed in our study. However, clinical observation suggests that our pragmatic approach of influencing AP frequency by the simple means of visual demonstration of the angiographic result of PCI has a strong effect on the patients. The ISCHEMIA trial revealed relevant symptomatic improvement in patients with more severe AP [19]. Placebo- and sham-controlled trials have shown that large parts of the treatment effect of conservative and interventional therapeutic strategies for AP can be ascribed to context factors such as the one employed in this pilot study. Thus, we think it is reasonable and realistic to expect a difference of 10 points with a standard deviation of 20 between the control and interventional groups regarding the quality of life scale of the SAQ (effect size of *d* = 0.5 (medium effect)). This difference would also be highly clinically relevant. To show an effect size of *d* = 0.5 with a power of 80% (*β* = 0.2) at a two-tailed significance level of *α* = 0.05, *n* = 64 patients need to be included in each group. With an estimated drop-out rate of 10%, a total of *n*_total_ = 144 patients need to be recruited.

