### Assignment of interventions: allocation

#### Sequence generation {16a}

Patients who fulfill the inclusion and exclusion criteria will be randomized in a 1:1 ratio stratified for daily or not daily AP episodes by a computer-generated random number list.

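### The angina-frequency subgroup (at most 2 episodes per week) meets the entry criterion (at least 2 per week) at a single value, so it cannot separate low from high angina frequency

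*Protocol article*

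**What the plan says.** Three parts of the protocol article set a cut-off on angina frequency.

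- **Entry.** The inclusion list in Eligibility criteria {10} sets a minimum of two episodes per week. The abstract (Design and methods) agrees: "patients with a frequency of AP ≥ 2/week will be randomized 1:1".
- **Randomisation.** Sequence generation {16a} has patients "stratified for daily or not daily AP episodes", and Participant timeline {13} uses the same daily versus not-daily split. The abstract words the factor differently: "stratified for AP frequency > 1/day".
- **Subgroup.** Methods for additional analyses {20b} says: "Further group analyses will be stratified by frequency of AP ≤ 2/week and severity of CAD". The same section adds a subgroup with dominant dyspnea.

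The main model, in Statistical methods {20a}, is an ANCOVA of each endpoint on treatment and sex, adjusted for the baseline value, stent number and baseline Canadian Cardiovascular Society score.

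**The concern.** A subgroup by angina frequency is presumably meant to ask whether the picture printout works differently in patients with little and with much angina. For that, the cut has to fall inside the range of frequencies that the trial admits. This one falls on the lower edge of that range.

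The trial is described as a pilot to inform a later confirmatory study, and whether the effect varies with angina burden bears on whom that study should enrol. A stated cut-off that cannot be used sensibly will also have to be changed at some point. In an open-label trial that is already recruiting, a change made late could be suspected of being driven by the data.

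**Working it through.** **1. The plan's own sample size.** Inputs from Sample size {14}: "a difference of 10 points with a standard deviation of 20", 80% power, "at a two-tailed significance level of *α* = 0.05", 1:1 allocation and 10% drop-out.

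- Normal approximation: n per arm = 2 × (1.960 + 0.842)² × 20² / 10² = 62.8, rounded up to 63.
- Two-sample t-test: 63.8, rounded up to 64 per arm (power at 64 per arm: 80.1%).
- Drop-out: 64 / 0.9 = 71.1, rounded up to 72 per arm, so 144 in total.

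The stated 64 per group and 144 in total reproduce. Nothing below disputes them.

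**2. The two cut-offs side by side.** Let F be baseline angina episodes per week.

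- Eligible: F ≥ 2.
- Subgroup: F ≤ 2.
- Eligible and in the subgroup: F = 2, and no other value.
- Eligible and outside it: F > 2.

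A patient with three episodes a week is thus grouped with one who has several a day. No section admits patients below 2 per week, and none says that the subgroup is defined at a time other than baseline.

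**3. What the size would be.** The article does not give the share p of patients at F = 2, so p is an assumption, shown over a wide range. With 128 evaluable patients and SD 20:

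- patients per arm in the subgroup: a = 64p; in the remainder: b = 64(1 − p)
- 95% CI half-width for the effect in the subgroup: 1.96 × 20 × √(2/a)
- power for a 10-point effect in the subgroup: two-sample t-test, d = 0.5
- SE of the difference in effect between strata: 20 × √(2/a + 2/b); power for a 10-point difference: Φ(10/SE − 1.96)

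| Assumed p | Patients at F = 2 | Per arm | CI half-width (points) | Power, effect in subgroup | Power, 10-point difference in effect |
|---|---|---|---|---|---|
| 5% | 6.4 | 3.2 | 31.0 | 8% | 9% |
| 10% | 12.8 | 6.4 | 21.9 | 13% | 13% |
| 20% | 25.6 | 12.8 | 15.5 | 23% | 20% |
| 30% | 38.4 | 19.2 | 12.7 | 33% | 25% |
| 50% | 64 | 32 | 9.8 | 50% | 29% |

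Check of the last row: SE = 20 × √(2/32 + 2/32) = 7.07; 10/7.07 − 1.96 = −0.546; Φ(−0.546) = 0.293.

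The table shows how far the subgroup's size and precision depend on p. It does not show that this cut is worse powered than another. An even split gives the highest power for a difference in effect, and that is still only 29%.

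**4. The randomisation factor.** Daily versus not daily lies inside the eligible range. Its definition is not settled, though: a patient with exactly one episode a day is in the upper stratum under the daily wording and in the lower one under the abstract's more-than-once-a-day wording.

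**The case against.** Several points on the other side have weight.

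- **Near-empty stratum.** A reader might infer that the subgroup is nearly empty and its complement nearly the whole trial, so that the question cannot be answered at all. The article does not support this. It gives no share at exactly 2 per week, and if half the patients sat there the stratum would be half the trial. What stands at any share is that the lower stratum is one value at the entry boundary.
- **Separate significance tests.** A reader might infer that p-values within each subgroup will be compared and a differential benefit claimed. The text says only that analyses are stratified. Whether an interaction is fitted is a detail that an analysis plan commonly settles, so its absence is no fault here.
- **A cut other than the randomisation factor.** This is not an error in itself. A subgroup on any baseline variable remains a randomised comparison, and vessel number and dominant dyspnea are not randomisation factors either. Using the stratum is a preference.
- **Low power.** This does not count against this cut in particular. Additional analyses in a pilot will be imprecise, and so would the replacement.
- **Another intended meaning.** The cut may be a slip for a different sign or number, or may refer to follow-up. The article does not say. A follow-up definition would make it a post-randomisation subgroup, which is a problem of its own.

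None of this removes the conflict between two stated cut-offs. It is also not a detail left to another document, because the article fixes the value itself.

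**Conclusion.** The point holds in a limited form. As written, the low-frequency stratum consists of eligible patients at exactly 2 episodes per week, and the split cannot tell low from high angina frequency. This follows from the two stated cut-offs alone, provided that both refer to baseline frequency and that the entry criterion is applied as written.

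The practical size cannot be fixed from the article. Over an assumed share of 5% to 50%, the stratum has about 6 to 64 evaluable patients and a 95% CI half-width of about 31 down to 10 points, against a planning effect of 10 points.

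The reach is one factor in one additional analysis. The primary and secondary ANCOVAs, the sample size, and the vessel-number and dyspnea analyses are unaffected. It is worth correcting before any outcome comparison by arm, but it does not threaten the trial.

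**What to change.** 1. Reconcile the additional-analyses section with the eligibility criteria by replacing the cut-off with one inside the eligible range, stated as baseline angina frequency. The preferred choice is the randomisation stratum, daily versus not daily, because it is recorded for every patient before allocation and is balanced by design.
2. Before that, state one definition of the stratum. The abstract's wording and that of the sequence-generation and timeline sections must be brought into line with what the randomisation list actually uses.
3. Preferably, estimate the difference in effect by adding the stratum and a treatment-by-stratum term to the planned ANCOVA. Report the effect in each stratum and their difference with 95% confidence intervals, labelled exploratory.
4. Date the change, and make it before outcomes are compared by arm.

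The cost is a few sentences in the protocol or analysis plan. No new data are needed, since angina frequency is already collected for eligibility and randomisation, and the sample size does not change.

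### The angina-frequency subgroup is cut at AP ≤ 2/week although entry requires AP ≥ 2/week, so one side of the split can hold only patients with exactly two episodes a week

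*Protocol article*

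**What the plan says.** Three places in the protocol article set a threshold on angina frequency.

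- **Entry.** The abstract (Design and methods) says: "One hundred forty four patients with a frequency of AP ≥ 2/week will be randomized". Eligibility criteria {10} lists the same minimum of two episodes a week among the inclusion criteria.
- **Randomisation.** Sequence generation {16a} has patients "randomized in a 1:1 ratio stratified for daily or not daily AP episodes by a computer-generated random number list". The participant timeline {13} also uses daily versus not daily. The abstract words the stratum differently: "One hundred forty four patients with a frequency of AP ≥ 2/week will be randomized 1:1 stratified for AP frequency > 1/day".
- **Additional analyses.** Section {20b} says: "Further group analyses will be stratified by frequency of AP ≤ 2/week and severity of CAD (> 1 vessel affected"). It adds a subgroup of patients whose dominant symptom is dyspnea. No other analysis by angina frequency is planned.

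The article nowhere allows entry below two episodes a week, gives a baseline distribution of angina frequency, or says that the {20b} cut refers to any time other than baseline.

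**The concern.** A subgroup cut should divide the enrolled population into groups that differ meaningfully on the characteristic of interest. Here the upper limit of the subgroup equals the lower limit for entry. The lower group is therefore not a range of less symptomatic patients but one value at the edge of eligibility, set against every higher frequency from three a week to several a day.

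Sections {14} and the Discussion say that the pilot is to supply parameter estimates for a confirmatory trial. Whether the effect depends on angina burden is a natural question for that trial, and {20b} contains the only planned look at it. Followed as written, that look cannot separate moderately from severely symptomatic patients, because both fall in the same group.

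**Working it through.** **1. Overlap of the two rules.** {AP ≥ 2/week} ∩ {AP ≤ 2/week} = {AP = 2/week}. The complement among eligible patients is {AP > 2/week}. This step needs no assumption beyond reading {20b} as baseline frequency.

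**2. Other readings of {20b}.**
- If the sign is a slip for ≥ 2/week, the subgroup is the whole trial and nothing is stratified.
- If follow-up frequency is meant, the split is on a post-randomisation variable that the intervention is expected to change, since Objectives {7} hypothesises a reduction in angina. {20b} does not say this.
- If the number is wrong or comes from another eligibility rule, the article does not show which value was intended.

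**3. The plan's own sample size.** Section {14} says it is reasonable to "expect a difference of 10 points with a standard deviation of 20 between the control and interventional groups", so d = 10/20 = 0.5, with 80% power and two-sided α = 0.05. The two-sample t-test gives 63.77, hence 64 per group (power 0.801). With 10% drop-out, 64/0.9 = 71.1, rounded up to 72 per group, 144 in total. The plan's figures reproduce, and the evaluable number is 2 × 64 = 128.

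**4. Illustrative size of the stratum.** The share with exactly two episodes a week is not given. Assumption: the number of episodes above two is geometric with mean m, so P(exactly 2) = 1/(1 + m). The half-width of the 95% confidence interval for the treatment difference within the stratum, with n per arm, is t(0.975; 2n − 2) × 20 × √(2/n).

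| m | Share | Patients of 128 | n per arm | Half-width (points) |
|---|---|---|---|---|
| 3 | 25% | 32 | 16 | 2.042 × 7.07 = 14.4 |
| 5 | 17% | 21 | 10.7 | 2.091 × 8.66 = 18.1 |
| 8 | 11% | 14 | 7.1 | 2.174 × 10.61 = 23.1 |

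**5. The same calculation for the randomisation stratum.** Assumption: 30% to 50% have daily angina.

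| Daily share | n per arm, smaller cell | Half-width (points) |
|---|---|---|
| 30% | 19.2 | 2.027 × 6.45 = 13.1 |
| 50% | 32 | 1.999 × 5.00 = 10.0 |

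**6. Precision of the interaction.** Whether the effect varies with frequency is a question about the difference between the two subgroup effects. Its half-width is t(0.975; 124) × 20 × √(2/n₁ + 2/n₂), with n₁ + n₂ = 64 per arm and t = 1.979.
- Cut at two a week, 25% share (16 and 48 per arm): 1.979 × 8.16 = ±16.2. At 11% (7.1 and 56.9): 1.979 × 11.25 = ±22.3.
- Daily versus not daily, 50% (32 and 32): 1.979 × 7.07 = ±14.0. At 30% (19.2 and 44.8): 1.979 × 7.72 = ±15.3.

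These figures ignore any gain from covariate adjustment, which would apply to both cuts.

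**The case against.** The strongest case against is that this is one exploratory analysis in a pilot powered only for the overall comparison. {20b} claims no power for its subgroups, so a wide interval in a small cell is normal and not in itself a defect. That stands: the fault is the conflict between the cut and the entry rule, and the precision figures only illustrate it.

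Three stronger readings are tempting and are not supported.

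- **That the stratum is close to empty, or that the other side is nearly the whole trial.** The share is unknown. The illustrative model gives up to 25%, and patients could cluster at the entry threshold and make it larger.
- **That the subgroup lacks randomisation balance because it is not the stratification factor.** Randomisation balances the arms in expectation within any baseline subgroup. Stratification only limits chance imbalance. The vessel-number and dominant-dyspnea subgroups are not randomisation strata either.
- **That the pilot therefore cannot tell a confirmatory trial whom to enrol.** {20b} also plans those two other subgroups, which this point does not touch.

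It is also fair to say that the article does not reveal what {20b} was meant to say. The randomisation stratum is one candidate among several, so reconciliation must come before replacement.

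**Conclusion.** The inconsistency is certain for a baseline reading, and no other part of the article resolves it. As written, the only planned angina-frequency subgroup sets the single entry-limit value against all higher frequencies. It says little about whether the effect varies with angina frequency.

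The size is illustrative only. It rests on an assumed share of 11% to 25%, the plan's SD of 20 and 128 evaluable patients. On that basis the cell holds about 14 to 32 patients, and its interval is wider than the planned difference of 10 points throughout that range. The primary endpoint, its ANCOVA, the intention-to-treat rule and the sample size are not affected. The point deserves correction because the error is plain and cheap to remove, not because it threatens the main result.

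**What to change.** 1. Reconcile the entry rule (abstract and Eligibility criteria {10}) with the cut-off in {20b} before analysis, and state that the subgroup variable is baseline angina frequency.
2. Unless another baseline cut-off was intended, replace the ≤ 2/week cut in {20b} with the randomisation stratum, daily versus not daily, as defined in {16a}.
3. Analyse it with the ANCOVA of {20a}, adding the stratum and a treatment-by-stratum interaction, and report the interaction estimate with its confidence interval.
4. Align the abstract's description of the stratum (more than once a day) with {13} and {16a}. An angina frequency of exactly once a day falls on different sides under the two wordings.

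The cost is a few lines of text. The stratum is already recorded at randomisation, so no patients, visits or data items are added. The article reports recruitment still under way, so the cut could be settled before results are seen; a later change could look post hoc.

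The downside is that the replacement is also exploratory and imprecise: about ±10 to ±13 points in the smaller cell, and about ±14 to ±15 for the interaction, if 30% to 50% have daily angina. Its main gain is a split between two ranges of frequency that can be interpreted; the gain in precision is modest.

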#### Methods in analysis to handle protocol non-adherence and any statistical methods to handle missing data {20c}

Data will be analyzed using the intention-to-treat principle. Crossover in our study would mean that patients in the control group have access to the angiogram of their PCI. However, these data are not routinely sent to other hospitals, primary care physicians, or care givers. Therefore, we expect the crossover rate to be very low.

#### Plans to give access to the full protocol, participant-level data, and statistical code {31c}

The datasets generated and analyzed during this study are available from the corresponding author on reasonable request.

### Oversight and monitoring

#### Composition of the coordinating center and trial steering committee {5d}

The coordinating center is the University Heart Centre Regensburg, Department of Internal Medicine II, University Hospital Regensburg, Regensburg, Germany. In each participating center, a lead investigator (cardiologist) will be identified, to be responsible for identification, recruitment, data collection, and completion of CRFs, along with follow-up of study patients and adherence to study protocol. To ensure optimal quality control regarding GCP-compliant data management, monitoring, and biometry, the Centre for Clinical Studies at the University Hospital Regensburg is part of the trial.

#### Composition of the data monitoring committee, its role, and reporting structure {21a}

The data monitoring committee consists of the key persons for conducting this trial ([name], [name], and [name]) and will maintain monthly meetings to discuss the progress and possible harms of this trial. Stopping rules include slow recruitment and life-threatening events, such as heart failure.

#### Adverse event reporting and harms {22}

This trial does not include the application of medicinal products or medical devices. Thus, no formal adverse event reporting is implemented. Nevertheless, as described above in **{21a}**, the progress of the trial conduct including potential harms is regularly discussed within the trial team.

#### Frequency and plans for auditing trial conduct {23}

Independent monitoring is provided by the Centre for Clinical Studies at the University Hospital Regensburg according to a pre-specified monitoring plan.

#### Plans for communicating important protocol amendments to relevant parties (e.g., trial participants, ethical committees) {25}

Any modifications to the protocol which may impact the conduct of the study and potential benefit of the patient or may affect patient safety, including changes of study objectives, study design, patient population, sample sizes, study procedures, or significant administrative aspects, will require a formal amendment to the protocol and approval by the local Ethics Committee prior to implementation and will be brought to the attention of the health authorities in accordance with local regulations.

### Dissemination plans {31a}

The papers presenting the results of this trial, especially baseline characteristics, and data of both follow-ups will be reviewed and approved by [name], [name], and [name].

## Discussion

Symptoms of stable CAD are currently often insufficiently controlled and have been shown to be highly prone to placebo interventions and modulation of context factors. Directly influencing these factors probably offers a means to reduce disease burden and improve QoL in this patient group. The PLA-pCi-EBO-pilot-trial examines the effects of visual demonstration of successful PCI in patients with stable CAD/CCS.

Daily clinical experience suggests that the integration of the patient into the decision-making process and appropriate, yet sufficiently detailed explanation of procedures and their results markedly improve therapy satisfaction and outcomes. An easy technique by which to achieve this is visual demonstration of test and therapeutic results, e.g., graphs of blood test results, x-ray images, etc. This assumption is derived from clinical experience and scarce scientific data exists to support this notion. Visualization of cardiovascular risk using risk scores, color-coded charts, graphs, and icons have been shown to alter patients’ behavior and reduce cardiovascular risk factors [25, 26]. These assumptions of the power of visualization were highlighted and confirmed by the VIPVIZA trial. In this Swedish trial, a stylized picture of patients’ carotid status, plaques, and stenosis as detected by ultrasound were shown and handed out to the patients. This led to a significant reduction of cardiovascular risk (Framingham risk score, European systematic coronary risk evaluation SCORE) in the 1-year follow-up [16]. The EISNER trial took a similar approach by assessing the effects of coronary artery calcium scanning on coronary risk factors. Patients that were randomized to coronary artery calcium scanning had a lower Framingham risk score compared to the control group in the 4-year follow-up [27]. These studies illustrate that visualization may constitute a potent means to alter patients’ cardiovascular risk, probably by altering lifestyle decision and improving adherence to medical treatment.

Comparable results were also found in oncology. In a randomized controlled trial (RCT) on patients with breast cancer, the intervention arm involved a graphic quality of life profile directed towards the patients’ treating physicians, whereas the control arm did not receive this visual aid. Half a year after the start of treatment, patients in the intervention arm reported better quality of life than patients in the control arm [28]. A recent RCT on patients with colorectal cancer confirmed this finding [29].

The PLA-pCi-EBO-pilot-trial aims to utilize these and other observations and translate them to improve outcomes of patients with stable CAD. This is especially relevant as this pathology represents a disease that is highly prevalent, limiting, and often difficult to treat. More than one third of patients in the COURAGE trial were still suffering from chest pain and dyspnea on exertion despite optimal treatment after 1 year [4]. Many trials investigating strategies to reduce disease burden have demonstrated a high susceptibility of AP for sham medication or interventions. Trials studying medical interventions in order to treat symptomatic patients frequently report highly relevant reductions in AP frequency in the placebo group [6, 7]. The ORBITA trial, a seminal work investigating the role and effects of PCI in patients with stable angina in a randomized, sham-controlled fashion, showed no difference between placebo and intervention groups for exercise testing, angina, or quality of life [8]. This study indicates that a relevant amount of the improvement after PCI might be attributed to the placebo effect and context factors. However, it has to be noted that the ORBITA trial only investigated one vessel disease in a highly selected, rather oligosymptomatic patient group and that there is a large debate on how these results should be interpreted and what they mean for clinical practice [30]. Major criticisms included that the follow-up time was rather short and a large number of patients crossed over from the placebo group to the PCI group.

Finally, the primary endpoint of this study consists of QoL in patients with CCS which is also considered to be related to the degree and the location of coronary stenosis. However, one major aim of PCI in CCS is symptomatic relief irrespective of specific lesion criteria [2]. The effect of PCI can be divided into measures caused by relief of a pathological mismatch which is certainly dependent on the initial problem, i.e., lesion specifications. However, as in any other medical intervention, this effect is accompanied by changes in disease perception and central pain processing (see the “Introduction” section). Therefore, we do not believe that the effect of our intervention—or placebo in general—is limited to specific lesions but rather relies on modulating the individual response of the participant, e.g., by improving disease perception, confidence in the treatment, and by reducing anxiety.

A picture conveys the information about the patient’s vascular status much more readily than explaining it in theory. Thus, demonstration of the results of the angiography is a possibility to positively alter context factors. Many practitioners already employ this method directly in the catheterization laboratory to explain the complex procedure. However, patients are often overwhelmed when this information is presented to them directly after the intervention. Routine visual demonstration after the PCI is not practiced yet. Our study does not exclude patients who have already been demonstrated the angiographic result in the catheterization laboratory as our aim is to evaluate the effect on top of this brief visual demonstration. However, it will be registered in our study if the physician has already shown the patient angiographic pictures during the intervention. Additionally, patients receive a printout of their angiography so that they have a reminder of the successful intervention after hospital discharge. The follow-ups include evaluation if and how often the patient has looked at the printouts after hospital discharge. As education might influence patients’ susceptibility for our intervention and understanding of the PCI procedure, this trait will also be registered. It is reasonable to assume that not every patient will profit from visual demonstration. Our study will include evaluation of a simple score to a priori estimate the success of our intervention.

Every medical encounter is characterized by a highly specific patient-clinician relationship. Although it is difficult to assess the precise effect of this relationship on medical outcomes, a meta-analysis of randomized controlled trials examining different communicational interventions found a small yet significant effect. The effect size was comparable to the reduction of myocardial infarction rates when using aspirin [15]. The placebo effect is moderated by stable personality traits such as optimism [14], empathy [12], and reward responsiveness [14], as well as transient psychological factors such as expectations [12], learning [12], or emotions [13]. Improvement of communication can positively influence these transient factors. Our study aims to elicit the placebo effect by modifying the context factors of PCI. We employ the German version of the revised Life Orientation Test [17] to assess the impact of dispositional optimism on the effect of visual demonstration.

Dyspnea is not part of the definition of angina pectoris; however, a substantial part of patients with CAD present with dyspnea as the dominant symptom together with atypical chest pain [24]. The latest update of the ESC guideline on stable CAD/CCS acknowledges this fact and highlights dyspnea as an important symptom of CAD [2, 3]. Clinical experience suggests that patients presenting with dyspnea as the main symptom are less susceptible to conventional medical or interventional treatment of CAD. This group therefore shows an increased need for additional treatment options and might especially benefit from alterations of context factors as are examined in our study design. Therefore, we additionally investigate changes of the NYHA classification at the time of both follow-ups. The time frame of the telephone interviews was chosen to assess for short-term effects after 1 month when the memory of the visual demonstration is supposedly still vivid. However, patients often do not recommence their normal daily activities directly after hospital discharge and therefore may not have had sufficient time to experience the full effects of PCI or of the visual demonstration. The 6-month interval was chosen to account for this and to measure possible lifestyle-induced changes in outcome.

The PLA-pCi-EBO-pilot-trial is designed as a pilot study to allow for precise parameter estimation for a subsequent confirmatory study. The determination of the study group size was based on both clinical and methodological considerations as well as on empirical facts since there are no clear reference points in the literature for this kind of investigation. Nevertheless, our considerations are informed enough to qualify this project as a pilot study that may set the stage for a large-scale trial with a definitive clinical impact. Clearly, obtaining the hypothesized effect justifies replication in a large-scale multi-center trial. Even if the hypothesized effect falls short of the conventional criteria of statistical significance, we may gain valuable information for designing a more definitive trial.

Quite generally, we believe that the subject of this study is highly relevant as it examines a simple, cost- and time-efficient, virtually side-effect-free tool to alleviate disease burden in the large and growing group of patients suffering from symptomatic stable CAD/CCS which has the potential to change the daily routine in the catheterization laboratory.

